## Abstract

**Background:**

Significant gaps exist in education for prospective and new parents, especially for some of the most vulnerable families. Prospective parents would like more information during pregnancy to prepare them for parenting, and need access to trusted and quality information.

The Royal Women’s Hospital (the Women’s) in Melbourne, Australia, a large tertiary referral maternity hospital, developed a parenting education kit known as ‘*Growing Together*’. The kit, designed to guide prospective and new parents from conception until 1 year after birth, includes three components: an A4 sized book, a specifically designed ‘App’ and a children’s story book. We aim to evaluate the impact of the kit on a range of outcomes.

**Methods:**

A two-arm cluster randomised controlled trial will be used. Antenatal clinic days will be randomised to either the intervention or standard care arms. Women in the intervention arm receive the kit at their antenatal booking visit. Women in the standard care arm receive the standard information resources at the Women’s. Analyses will be by intention to treat. Inclusion criteria: primiparous women with adequate English-speaking ability and ≤ 30 weeks’ gestation at first pregnancy booking appointment.

The primary outcome of the study is the ‘experience of motherhood questionnaire’ (EMQ), a 20 item validated self-report measure, ranging from 0 to 80, with lower scores indicating better maternal health and wellbeing. To detect a 10% difference in new mothers scoring ≤40 between women who have received the kit (60%) and those who have not (50%), would require 408 per group (total of 816 women) with 95% confidence and 80% power. Allowing for loss to follow up, we aim to recruit 1000 mothers. Secondary outcomes include parents’ views and experiences of their care and of the kit during pregnancy and after the birth, parental attachment, knowledge, confidence, wellbeing and health-seeking behaviour; and emotional, developmental and physical health of the infant. Survey data will be collected from mothers at 2, 6 and 12 months postpartum and partners at 6 months.

**Discussion:**

This study will provide much needed high-level evidence on the impact of a comprehensive education resource for new parents.

**Trial registration:**

ANZCTRN12615000270516 - Retrospectively registered (23/03/2015); trial started on 16 March 2015.

## Background

There is growing recognition by health care providers that prospective parents would like more information during pregnancy to prepare them for parenting [1–3]. Once families leave hospital, the home environment is crucial to a child’s physical, cognitive and emotional development [4]. New mothers and their partners must learn ‘on the job’, often with little preparation beyond what they have observed of families around them and what they can gather from (sometimes conflicting) multiple information sources. Parents need direct access to quality information to help prepare them for their unique role in shaping their child’s future.

### Information needs of new parents

Information currently available for expectant and new parents varies widely in quality and accessibility, and may be sought from midwives, obstetricians, general practitioners (GPs), family, friends, Maternal and Child Health nurses (MCHNs), books, websites and social media. A national study on the information needs of Australian parents found that awareness of the range of available information was generally low, and that parents’ information needs were only partly addressed by the information they found [5]. Another Australian study involving antenatal educators and new mothers found that mothers rarely receive information beyond labour and birth management and breastfeeding in antenatal classes [6]. A recent systematic review and meta-synthesis of 12 qualitative studies reported that new parents often felt inadequately prepared for the early parenting period, and recommended that antenatal education classes place equal emphasis on the antenatal and postnatal periods [1]. A national review of the evidence for parenting interventions in Australia indicated that there are very few evidence-based programs which target child development, no programs for parents with disabilities or mental health issues, and no programs for teenage parents [7].

### Practical issues related to feeding and sleep

New parents also face many practical issues. Many experience anxiety and concern about infant feeding [8], the amount and pattern of their infant’s sleep [9], and about strategies for settling their infant and managing crying. Parents with concerns about their infant’s sleeping, feeding and crying are more likely to seek medical assistance in the belief that something is wrong [10], and are at increased risk of postnatal depression and fatigue [9, 11]. There is now growing evidence that anticipatory guidance provided in the early stages of parenthood helps parents to establish good infant sleep and feeding habits, reduces parent distress about normal infant crying, and reduces postnatal depression symptoms [12–14]. Despite this promising evidence, methods for ensuring the timely provision of such advice at a population level are lacking.

### The California kit for new parents

The California kit for New Parents was developed and piloted in the United States in 2001, and has since been distributed, at no charge, to more than two million Californian families [15]. The kit is made up of a DVD about the emotional and cognitive development of infants and children, a children’s book, and a parenting guide. It is available in six languages [15], and has been adopted by authorities in Arizona, Pennsylvania, Alabama and Kentucky [4].

Evaluations of the kit found that providing information (e.g. about antenatal care, early childhood learning and development, infant nutrition and access to services) to expectant and new parents resulted in significant improvements in parenting confidence, knowledge and behaviour [16]. Short- [4] and long-term [15] evaluations found that the kit had a positive impact on parents’ knowledge, attitudes and behaviours: 87% of mothers used the kit within 2 months of receiving it and 53% reported sharing it with their partner. A year after receiving the kit the majority of mothers reported using the kit multiple times; and 94% of mothers reported that the kit was helpful with a wide range of parenting issues. Mothers who received a kit demonstrated improved parenting practices in child development, infant feeding, early literacy, child safety, health care and access to local resources compared with mothers who did not receive a kit [4]. Knowledge gains were high for all parents who received a kit; with the highest among women who received the kit before the baby was born, and for women who spoke Spanish [4]. Parents reported liking the option of choosing from a variety of formats, identifying with people and parenting practices in the DVDs, and feeling empowered by seeing new ways of parenting.

### The ‘parenting kit – Growing Together – at the Women’s hospital

Based on the California kit for New Parents, a parenting kit was developed by the Royal Women’s Hospital (The Women’s) in Melbourne, Australia, a large tertiary referral maternity hospital, to guide prospective and new parents from conception until their child is 1 year of age, titled “*Growing Together*”. Drawing on existing research and the resources already available, *Growing Together* aims to inform parents about the ages and stages of development from conception to 12 months. It provides practical information—from a single authoritative, trusted and non-commercial source—about health care, health promotion, child care and social support and links to Victorian and Australian Government funded parenting services, resources and information.

The Women’s undertook a community engagement process to develop and pilot *Growing Together*, with the aim of then evaluating its impact to determine if a single kit, such as that being developed could meet the needs of all parents.

The content and presentation of the kit was determined in consultation with parents and families; participatory design was integral to its development. Community consultations with a diverse range of families shaped the design and content of the kit, so that messages about the importance of safe and secure relationships, encouraging learning and responding to the individual infant’s personality right from birth are communicated in accessible and empowering ways [17]. There was also a greater focus on parents’ mental health than traditional resources aimed at prospective and new parents. The kit design is generic and not focused only on the Women’s Hospital. Therefore, if it is shown to be acceptable and effective, it could be rolled out more broadly.

There are three parts to the *Growing Together* kit:An A4 size book that covers the journey from conception to 1 year of age.A phone ‘App’ comprising four modules – one each for preconception, pregnancy, parenting, and one for health professionals. The ‘App’ is interactive, and has push notifications, videos and links to various appropriate sites and many other features.A children’s book written by Australian author Mem Fox, titled *Ten Little Fingers and Ten Little Toes,* is aimed at encouraging parents to read to their children, as well as containing what are considered to be important messages for parents.

The Growing Together book includes information about pregnancy and birth care options, different stages of the pregnancy and labour, care during pregnancy (including changing in the body and discomfort; relevant tests and screening; medicines, drugs and substances; important nutrients during pregnancy; when to contact hospital; emotional and mental health), labour and birth (e.g. preparing for labour and birth, when to go to hospital, pain relief in labour) and care after birth (e.g. breastfeeding; safe sleeping; sex and contraception; postnatal mental health).

Funding from the Victorian Government was granted to the Women’s to develop, and then distribute 2000 *Growing Together* kits and evaluate the outcomes. A team from Judith Lumley Centre (JLC) at La Trobe University in Melbourne, Australia, was engaged to undertake an evaluation of *Growing Together*, measuring various outcomes including women’s experience of motherhood, attachment, infant development, and parenting confidence as well as the views and experiences of health professionals.

This paper describes the study protocol for the kit evaluation.

## Methods/design

We will undertake a two-arm cluster randomised controlled trial (RCT) to explore the impact of the *Growing Together* kit on women’s experience of motherhood and a range of parenting-related outcomes, and to compare these with the outcomes and experiences of women who received the usual hospital information (standard care). We will also explore parents’ views of the kit.

### Randomisation and recruitment

The Women’s has four geographically-based maternity care teams, each of which has one antenatal clinic day per week (Monday - Thursday). To reduce the risk of contamination, (as would be the case if individual women were randomised), individual clinic booking days will be randomised, so that all women booking on a randomised day will receive the kit. Individual randomisation is not pragmatic given the high potential for clinician errors (clinicians would have to change the information they give to individual women throughout any booking clinic). Additionally, women may notice other women receiving different information packages.

Randomisation will be undertaken by an independent statistician at the Judith Lumley Centre. Using a blocked randomisation technique, the clinic days will be randomly allocated throughout the recruitment period to either intervention or standard care. The randomisation schedule will be kept confidential, with only the project coordinator, PhD student and senior research midwife having access in order to plan staffing for the research midwives.

As it is clusters (i.e. clinic days) being randomised and not individuals, randomisation will be done in advance, to ensure equal proportions of the four clinic days are randomly allocated to standard care and the intervention over the estimated 22 week recruitment period. The recruitment period was predicted based on the average number of booking visits per week at the Women’s and an estimation of women’s eligibility. For various reasons (e.g. geographical variations in the number of women meeting eligibility criteria), some clinic days may meet their quota of eligible women in fewer recruitment days than others. For this reason, recruitment will cease in each clinic (maternity care team) when their quota is reached.

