### Eligibility criteria and processes

All eligible women booking for pregnancy care at the Women’s during the recruitment period will be included in the study. Inclusion criteria include primiparous women with adequate English-speaking ability (i.e. do not require an interpreter) and at ≤30 weeks gestation at first pregnancy booking appointment. Women will also be included if they had a previous stillbirth and no living children. The rationale for recruiting only primiparous women is that the information needs for first time parents are likely to be different than for parents who have already had a child.

To determine eligibility of women, prior to each randomised clinic day, the project coordinator or PhD student will screen all new booking histories to identify eligible women using the GP referral sheet, or available past history (Fig. 1). If identified as eligible, they are considered to be participants in the trial, in either the standard care or intervention arms as per the clinic randomisation schedule. Details of women who are identified as eligible (in either the intervention or standard care arms) will be entered into a password protected database with their estimated due date. These details will be used to facilitate the later checking of birth outcomes, mail-out of surveys and follow up phone calls at the specified data collection time points (described later). Births will be checked 2 weeks after the due date to ensure, as far as possible, that follow up contact occurs only with women who are discharged home with a live baby. The hospital’s electronic data systems will be used to facilitate this process.

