### Process evaluation measures

A number of strategies will be considered for process evaluation and to evaluate intervention implementation and uptake.

On the intervention recruitment days research midwives will be present to monitor the number of kits given. Kits will be attached to the history of eligible women; there will be only a limited number of kits distributed each day according to the pre-determined number of eligible women.

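### The two roles that screen women for eligibility also hold the advance allocation schedule, so entry into the trial is not concealed from the arm

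*Protocol article*

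**What the plan says.** Randomisation and recruitment makes the clinic day the unit of allocation and states that "randomisation will be done in advance, to ensure equal proportions of the four clinic days" go to each arm over an estimated 22 weeks. On access it says: "The randomisation schedule will be kept confidential, with only the project coordinator, PhD student and senior research midwife having access". The reason given is "in order to plan staffing for the research midwives".

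Eligibility criteria and processes describes how women enter: "prior to each randomised clinic day, the project coordinator or PhD student will screen all new booking histories to identify eligible women". The effect of that decision is immediate: "If identified as eligible, they are considered to be participants in the trial", in whichever arm the schedule gives to that day. The criteria are first-time motherhood (a previous stillbirth with no living child also qualifies), no need of an interpreter, and a gestation of at most 30 weeks at booking. They are read from the GP's referral sheet or from whatever past history is on file. The section requires all new booking histories to be screened and every eligible woman to be included.

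Ethical considerations adds that no individual consent is sought at entry.

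**The concern.** When clusters are allocated in advance, the cluster's arm is settled before its members are known. Protection against selection bias then depends on members being identified by someone who does not know the arm. Here the persons who identify them can know it, and their decision alone puts a woman in or leaves her out.

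Most of the criteria can be checked, but the check is made on papers that may be incomplete. A referral may leave parity, gestation or the need for an interpreter unclear, and someone must then decide. If such cases are settled differently on intervention and standard care days, even without intent, the arms differ before any kit is handed out. What is at stake is the comparability of the arms, which is what randomisation is meant to secure.

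**Working it through.** **1. The roles side by side**

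| Role | Holds the advance schedule (Randomisation and recruitment) | Screens for eligibility (Eligibility criteria and processes) |
|---|---|---|
| Project coordinator | yes | yes |
| PhD student | yes | yes |
| Senior research midwife | yes | not named |

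Both screening roles hold the schedule. The order of events is: days randomised for the whole period, schedule open to the three roles, histories screened before each day. So the arm can be known at the time of screening. The article does not describe screening without the arm, a list closed before the arm is looked up, or a check by someone without access. The stated purpose of access, staffing, does not require a screener to know the arm while judging a history.

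**2. The plan's own figure**

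The point itself rests on no figure. The illustration below uses the Sample size section's 50% against 60%, 408 per group, 95% confidence (taken as two-sided 5%) and 80% power. The two-proportion formula gives

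n = [1.96·√(2·0.55·0.45) + 0.842·√(0.50·0.50 + 0.60·0.40)]² / 0.10² ≈ 387.3, so 388.

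With the continuity correction, (387.3/4)·[1 + √(1 + 4/(387.3·0.10))]² ≈ 407.1, so 408. The plan's figure is reproduced.

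**3. Illustration of size (assumed values)**

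The documents give no rate of wrongly omitted women. Suppose the kit has no effect and the true rate of scoring 40 or less is 50% in both arms. Let a fraction f of *all eligible women* be omitted in one arm only, and let q be the share of those omitted who would have scored 40 or less. The rate among those kept is

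p = (0.50 − f·q) / (1 − f).

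For q = 30%: f = 5% gives 0.485/0.95 = 0.5105, and f = 10% gives 0.470/0.90 = 0.5222.

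The type I error is the probability that a two-sided 5% test with 408 per arm rejects. With d = p − 0.50 and p̄ = (p + 0.50)/2, it is Φ[(d − 1.96·se₀)/se] + Φ[(−d − 1.96·se₀)/se], where se₀ = √(2p̄(1−p̄)/408) and se = √(p(1−p)/408 + 0.25/408).

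| f | q | p | Spurious difference (points) | Type I error |
|---|---|---|---|---|
| 5% | 40% | 50.5% | 0.5 | 5.3% |
| 5% | 30% | 51.1% | 1.1 | 6.0% |
| 5% | 20% | 51.6% | 1.6 | 7.4% |
| 10% | 40% | 51.1% | 1.1 | 6.2% |
| 10% | 30% | 52.2% | 2.2 | 9.7% |
| 10% | 20% | 53.3% | 3.3 | 15.9% |

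The result depends strongly on f. If only a tenth of eligible women had doubtful papers (assumed) and 5–10% of those were omitted, f would be 0.5–1%. With q = 30%, p is then 0.4985/0.995 = 50.1% to 0.497/0.99 = 50.2%, a shift of 0.1–0.2 points. The sign is also assumed: omissions in the standard care arm would work against the kit.

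**The case against.** The strongest defence is that little is left to judgement. English is defined by the need for an interpreter, parity and gestation are facts, every booking history must be screened and every eligible woman included. With no consent step, neither persuasion by a recruiter nor a woman's knowledge of her arm can affect entry. Access is granted for staffing and does not prove that any decision was made with the arm in mind. The working order may be set out in the full protocol or in Fig. 1, which is not shown.

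Much of this stands, and it limits the likely size. It does not remove the point. The inclusion rule protects only if eligibility is judged the same way in both arms, and without a consent step the screener is the only gate. Nor is this a detail merely left out: the article states who sees the schedule and who screens, and the two lists overlap.

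Two stronger readings are tempting and are not supported:

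- A reader might infer that research midwives attend on intervention days only, so that wrong eligibility or non-attendance is noticed more in that arm. Process evaluation measures says "On the intervention recruitment days research midwives will be present to monitor the number of kits given". It does not say that they attend on no other days or that they check eligibility. The caption of Fig. 1 mentions non-attendance but does not show how it was handled by arm.
- A reader might infer that analysis cannot repair the bias because background data come from respondents alone. The article says that such data are collected in all surveys and interviews, not that this is their only source. It also plans adjustment for baseline differences and for demographic and birth factors. All that can be said is that adjustment reaches recorded characteristics and may be incomplete.

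**Conclusion.** The point holds in a limited form. As described, identification of participants is not concealed from the allocation, because both screening roles hold the schedule and no safeguard is stated. The documents show a risk, not that selection occurred, and they give no basis for its size. If 5–10% of all eligible women were omitted in one arm and 30% of those would score 40 or less, the shift is about 1–2 of the 10 points sought; with 20–40% it is 0.5–3.3 points. Smaller omission rates make it negligible. A reader should not infer that the bias could by itself produce the planned effect, since nothing in the range shown comes near 10 points. The weakness is worth correcting because it is avoidable at little cost.

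**What to change.** - Keep the advance schedule with the senior research midwife, who can plan staffing from it, and withdraw it from the project coordinator and the PhD student. A lock alone would not help while the screeners can see the schedule.
- Have the screeners complete each clinic day's eligible list in the existing database and lock it with a time stamp. Release that day's arm to them only afterwards, in time for kits to be attached before clinic.
- Correct eligibility errors found later by one record-based rule applied in the same way in both arms. Leave the post-birth exclusions in the 2 month survey section as they are.
- Report numbers screened, eligible and excluded, with reasons, by clinic day and arm. The article describes database entries only for women judged eligible, so a short record for each excluded woman would be an addition.

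The cost is a change of access rights, a lock on the database and lists finished slightly earlier.

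The trial registration entry gives a start on 16 March 2015, and 22 weeks from then runs to mid-August 2015, so recruitment may well be complete. In that case, report the same numbers as far as records allow and state plainly that the screeners had access to the allocation.

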### Sample size

The experience of motherhood questionnaire (EMQ), a 20-item self-report measure, has been used to determine the sample size [18] with the goal of reducing the proportion of women scoring low on the EMQ. A score of 40 on the EMQ is a typical median score for a sample of first time Australian mothers. We therefore expect 50% of women in the standard care to score 40 or less. To detect a difference of 10% (50% compared to 60%) scoring 40 or less between new mothers who have received the kit and those who have not would require 408 per group (total of 816 women) with 95% confidence and 80% power. Allowing for loss to follow up we therefore aim to recruit 1000 mothers. We do not anticipate needing to allow for any potential effect of clustering given we will ensure relatively equal numbers of women from the four geographically-based teams (i.e. the main factor which may introduce differences) will be allocated to both trial arms. Similarly, the clinical guidelines, models of care, and appointment length are all uniform across the four teams, thus minimising the potential for different influences based on team allocation. Where appropriate, we will adjust for demographic and birth outcomes.

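### Stopping each team at its quota leaves the planned within-team balance of arms expected but not ensured, and the analysis does not include team as a matter of course

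*Protocol article*

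**What the plan says.** Under Randomisation and recruitment, the protocol article describes four maternity care teams, "each of which has one antenatal clinic day per week (Monday - Thursday"). The clinic day is the unit of allocation: "Using a blocked randomisation technique, the clinic days will be randomly allocated throughout the recruitment period to either intervention or standard care". The schedule is prepared beforehand "to ensure equal proportions of the four clinic days are randomly allocated to standard care and the intervention over the estimated 22 week recruitment period". That section also expects teams to recruit at different speeds, so that "some clinic days may meet their quota of eligible women in fewer recruitment days than others", and concludes: "For this reason, recruitment will cease in each clinic (maternity care team) when their quota is reached". It does not give the size of the quota, say whether the quota counts both arms together, or link the stop to the end of a block.

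The Sample size section makes no allowance for clustering. Its reason is that similar (in its terms, relatively equal) numbers of women from each of the four teams will go to each arm, team being named as the main possible source of differences. It adds that guidelines, models of care and appointment length are the same in all four teams.

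The Data management and analysis section compares arms by chi-square tests and relative risks, and by t-tests or Mann-Whitney tests for continuous outcomes. A multivariate analysis is added where the women's demographic characteristics differ between arms. Team is not mentioned there.

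**The concern.** The balance is a property of the full schedule, but the stop is triggered by a count of women. A team that fills its quota before week 22 uses only the first part of its schedule, and that part need not hold equal numbers of intervention and standard-care days. The article expects some teams to finish early, so this is a foreseen event.

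If it happens, arm and team become associated to some degree. Team is the factor the article singles out, yet the planned comparisons would not correct for it: adjustment depends on observed demographic differences, and an uneven mix of teams may not show up as one. The factor that allocation is meant to balance is thus neither secured by the stopping rule nor a stated term in the analysis.

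**Working it through.** **1. The plan's own figure.** For 50% against 60%, two-sided 5%, 80% power:

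n = [1.960 × √(2 × 0.55 × 0.45) + 0.842 × √(0.25 + 0.24)]² / 0.10² = 387.3, or 388 per group. With continuity correction, (387.3/4) × [1 + √(1 + 4/(387.3 × 0.10))]² = 407.1, or 408 per group. The stated 408 (816 in total) is reproduced.

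**2. Planned pace.** 4 teams × 22 weeks = 88 clinic days; 1000/88 = 11.4 women per clinic day. An equal quota would be 1000/4 = 250 per team. A team at that pace needs about 22 days (250/11.4); a team seeing 16 women a day needs about 16 (250/16).

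**3. Upper limit from blocking.** With blocks of b days formed within a team, half to each arm, stopping anywhere leaves at most b/2 days of imbalance: 1, 2 or 3 days for b = 2, 4 or 6.

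**4. Simulation** (4,000 runs per setting). Assumptions not in the article: quota of 250 counting both arms, Poisson clinic-day sizes, a 22-week limit, team speeds of 16, 13, 11.4 and 10 women per day, blocks within team. The rows without a stop use 11.4 per day in all teams.

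| Setting | Largest day imbalance | Larger arm's share in a team, 95th percentile | Teams beyond 55:45 | Teams beyond 60:40 |
|---|---|---|---|---|
| Stop, blocks of 2 | 1 | 57% | 16% | 0.3% |
| Stop, blocks of 4 | 2 | 58% | 22% | 1.3% |
| Stop, blocks of 6 | 3 | 59% | 26% | 2.4% |
| Stop, one block of 22 | 7 | 60% | 28% | 5.3% |
| No stop, blocks of 2 or one of 22 | 0 | 56% | 11% | 0.1% |
| No stop, blocks of 4 | 2 | 58% | 22% | 1.6% |

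Blocks of 4 do no better without the stop, because 22 is not a multiple of 4. Over all teams together, the 95th percentile of the larger arm's share is 54% to 55% in the four settings with a stop.

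**5. One fast team, one 22-day block** (20,000 runs per setting, quota 250). The larger arm exceeds 60% in 1.4%, 8.7%, 17.1% and 24.1% of runs at 12, 14, 16 and 18 women per day. The arms differ by 2 or more days in 13%, 40%, 49% and 52%. With blocks of 4 the latter figures are 9%, 11%, 4% and 14%.

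**6. Power at 816 women** (no continuity correction): 82.0% at 50:50, 81.6% at 55:45, 80.4% at 60:40.

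**7. Bias, illustrated.** Let two teams have 45% and two 55% scoring 40 or less, with no kit effect. If the first two split 45:55 and the other two 55:45 (intervention:control), the intervention arm averages 0.45 × 0.45 + 0.55 × 0.55 = 50.5% and control 49.5%, a bias of 1 point. At 60:40 it is 51% against 49%, or 2 points. In general the bias is (2 × share − 1) × team difference. A team term removes it, because the arm difference within each team is zero.

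**The case against.** The sample-size section promises only relatively equal numbers, and a typical split of about 53:47 with short blocks meets that. Block size, block strata and the definition of the quota are details that an article may leave to the full protocol, and a quota counted by team and arm would fit the wording. This stands, and it is why the point concerns what is not ensured, not a balance shown to fail.

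A reader might infer large imbalances from the 17% and 24% figures. They need a single 22-day block and 16 to 18 women per day, against 11.4 implied by the plan; the article supports neither assumption. A reader might also infer that imbalance is always worst in the fastest teams. With blocks of 4 it is not: the figures by speed are 9%, 11%, 4% and 14%. Nor does a stop on a total count favour one arm; the imbalance is a chance one. Finally, some of those who hold the schedule also screen for eligibility, which may suggest that the stop could be steered. The article does not say who counts towards the quota, and nothing in it shows such steering.

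It can also be said that a covariate list belongs in the statistical analysis plan. That answers less, because the article itself fixes when adjustment happens: only where demographic differences are seen.

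**Conclusion.** The concern holds in a limited form. As written, the stopping rule does not ensure the within-team balance that the Sample size section relies on. With short within-team blocks the shortfall is at most 1 to 3 clinic days and adds little to ordinary variation in clinic size. It becomes material only with long blocks in teams that recruit fast. Power falls by less than 2 points even at 60:40, and bias is 1 to 2 points under an assumed 10-point difference between teams, against a target difference of 10 points. These sizes rest on an assumed quota of 250, Poisson clinic sizes and assumed team speeds.

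The firmer part is the analysis. Team is the factor that allocation is balanced on and that the article names as the main possible source of differences, so it should not enter only when demographic imbalance happens to be seen. Team balance, however good, says nothing about correlation among women booked on the same clinic day; that is a separate issue.

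**What to change.** **Analysis.** Include team (clinic weekday) as a pre-specified fixed term in all arm comparisons, whatever imbalance is observed: for example a relative-risk regression for the primary outcome and linear regression for continuous outcomes. The cost is three indicator terms and no extra data. This part can be adopted even if recruitment has closed.

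**Recruitment rule.** If blocks are short and within team, let a team that reaches its quota finish its current block before stopping, and make the schedule a whole number of blocks. Alternatively, define the quota by team and arm. Finishing a block costs at most b − 1 further days per team: 1, 3 or 5 for blocks of 2, 4 or 6. Kits are not limiting: 2000 are funded and about 500 are needed (half of 1000 women). With one 22-day block this change would amount to running the whole schedule, so it is worth making only with short blocks.

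Neither change deals with correlation within clinic days.
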